### 2.6. Randomization and Allocation

After the baseline preassessment visit (V0), participating families will be randomized into the eight study groups. The randomization sequence list will be generated using the Randomization.com website (http://www.randomization.com) (accessed on 13 September 2024) by an external researcher not involved in this study. Stratified randomization, employing blocking, will be conducted to achieve a 1:1:1:1:1:1:1:1 ratio for the 7 intervention groups and the control group; *n* = 60 families per block. Due to the nature of the study, the families and the research staff cannot be blinded to the intervention, although the investigators who will perform the data analysis will work under concealment of the assignment.

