## 2. Materials and Methods

### 2.1. Study Design and Setting

The SWITCHtoHEALTHY study is a parallel, randomized, single-blinded, and controlled multicentric nutritional intervention study. It aims to evaluate the effects of a multi-component intervention deployed at the family level, combining digital interactive tools and hands-on educational materials and activities with healthy and sustainable plant-based snacks, on the adherence to the MD pattern in 480 families with adolescents and children from three Mediterranean countries (Spain, Turkey, and Morocco), with 160 families per country. Secondarily, the effects of the multi-component intervention will be assessed according to lifestyle, anthropometric, dietary, sociodemographic, socioeconomic, and environmental indicators.

This study protocol was registered at ClinicalTrials.gov (NCT06057324) and is in accordance with the Helsinki Declaration and the Good Clinical Practice Guidelines on the International Conference of Harmonization. All the procedures described in the protocol, informed consent, and other documents have been reviewed and approved by the Ethics Committees of the three centers involved in the study: (1) Fundació Eurecat (study co-ordinator): Institut d’Investigació Sanitària Pere Virgili, IISPV (Ref. 135/2023); (2) Ethics Committee of Bursa Uludag University Faculty of Medicine Clinical Researches (Ref. 2023-23/29); and (3) Comité d’Ethique pour la Recherche Biomédicale (CERB), Université Mohammed V Faculté de Médecine et de Pharmacie de Rabat (preapproval). This protocol complies with the Standard Protocol Items: Recommendations for Clinical Trials (SPIRIT 2013 Statement and SPIRIT-AI extension) [32,33].

The 160 families recruited in each country will be randomly assigned into eight study groups (*n* = 20 families per group per country) according to a multi-component intervention including different combinations of the three study components (artificial intelligence (AI)-based app for all family; educational materials and empowerment activities for adolescents; and healthy plant-based snacks for children) and a control group that will receive basic Mediterranean guidelines for parents and their children (Figure 1).

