### 2.7. Sample Size

The sample size was calculated based on differences in MD adherence score (primary outcome) measured by MEDAS and KIDMED questionnaires. The sample size was estimated using the analysis of variance (differences between 8 study groups). It was assumed that the alpha value would be equal to 0.05 and beta 0.20, exactly as reported in previous studies [61], with a common standard deviation equal to 1.19. The minimum group size needed to detect a minimum increase of 1 point in the intervention group’s MEDAS compared to the control group is equal to 45 families per study group (15 families per country). The total sample is, therefore, 45 × 8 = 360 families. However, assuming a 25% drop-out rate, the minimum group size is equal to 60 families per study group (20 families per country). Overall, 160 families will thus be recruited per country after obtaining the approval of the Ethics Committee of each recruiting center and written informed consent from parents and adolescents.

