### 2.10. Statistical Analysis

#### 2.10.1. Univariate Data Analysis

The data obtained from families in this study will be evaluated via an intention-to-treat (ITT) analysis, including data from families who drop out of the study, and per protocol (PP), that is, those families who have completed the treatment plan and who have exactly followed the instructions of the trial protocol. The error level of 0.05 will be set as a limit of statistical significance. A data analysis will be performed using the Statistical Software for Data Science (STATA, College Station, TX, USA) version 17.0 [63].

Mean and standard deviation will be reported for normally distributed variables and quantiles (25th percentile, median, and 75th percentile) for non-normally distributed variables. The Kolmogorov–Smirnov test and the Shapiro–Wilk test will be used to test for the normality of variables. The resulting scores of adherence to the MD (measured from the MEDAS and KIDMED questionnaires) will be used to calculate the mean differences between each intervention group and the control group before (V1) and after interventions (V2). Multiple comparisons (V2 vs. V0 and V2 vs. V1) of mean differences before and after interventions will be undertaken to assess the independent effect of interventions. The normality of the differences will be checked and, depending on the results, the following contrasts will be performed: parametric statistics (three-factor ANOVA with post hoc tests using the Bonferroni correction and considering the interactions between the following factors: app, educational materials, and snack products) will be used for normally distributed variables to compare differences in means and nonparametric statistics (Kruskal–Wallis test) will be used for non-normally distributed variables. Lineal regression and Spearman’s method will be used to test for correlations between normal and non-normal outcome variables, respectively.

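### The stated block of 60 families cannot give eight equal groups or fill 160 families per country; separately, the primary three-factor ANOVA leaves out country

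*Protocol article*

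**What the plan says.** **Allocation.** Section 2.6 of the protocol article states: "Stratified randomization, employing blocking, will be conducted" "to achieve a 1:1:1:1:1:1:1:1 ratio for the 7 intervention groups and the control group", with "60 families per block". It does not name the stratification factor. Section 2.1 states: "The 160 families recruited in each country will be randomly assigned into eight study groups", at "20 families per group per country". Section 2.7 reaches the same numbers from the sample size calculation: 60 per study group, 20 of them from each country.

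**Analysis.** For normally distributed outcomes, Section 2.10.1 specifies a "three-factor ANOVA with post hoc tests using the Bonferroni correction and considering the interactions between the following factors: app, educational materials, and snack products". The fallback for non-normal outcomes is a Kruskal–Wallis test. Country appears in neither. Section 2.10.2 adds a stratified analysis by income, education and cultural background, to see how context affects the response to the interventions.

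**The concern.** There are two separate matters.

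1. A permuted block that holds eight arms equally must be a multiple of eight, and 60 is not. Nor do whole blocks of 60 fill a country's 160 families. As printed, the rule in Section 2.6 can deliver neither its own ratio nor the per-country group size in Sections 2.1 and 2.7, and nobody could reproduce the allocation from it.

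2. Group sizes are set within country, so country is the implied stratum, yet the primary model lists its factors and country is not among them. The authors themselves name differences between the three cultural areas as a possible influence on the results (Section 3), and the materials and snacks differ by country (Sections 2.3 and 2.3.3). If country explains part of the variation in change in adherence, that part stays in the error term.

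**Working it through.** **Inputs**
- Arms: 8, equal ratio (Section 2.6).
- Stated block: 60 families (Section 2.6).
- Families per country: 160, with 20 in each arm; three countries (Section 2.1).
- Evaluable group size 45 and drop-out 25% (Section 2.7).
- Share of the variance in change scores explained by country: not given; assumed 0 to 20%.

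**Step 1: reproduce the plan's group sizes.** 45/(1 − 0.25) = 60 per group; 60 × 8 = 480 families; 480/3 = 160 per country; 160/8 = 20 per group in each country. Sections 2.1 and 2.7 agree with each other.

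**Step 2: test 60 as a block size.**
- 60/8 = 7.5, so equal arms within a block are impossible. The nearest split is four arms of 7 and four of 8 (28 + 32 = 60).
- 160/60 = 2.67: two whole blocks use 120 families and leave 40.
- 480/60 = 8, the number of groups, and 20 × 3 = 60. The figure therefore matches the size of a study group.

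**Step 3: block sizes that would work.** A size must be a multiple of 8 and, if fixed, must divide 160: 8, 16, 32, 40, 80 or 160. Each gives exactly 20 families per arm in each country at randomisation. A mixture also works if it closes at 160, for example six blocks of 16 and eight of 8: 96 + 64 = 160.

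**Step 4: cost of leaving country out.** With balanced allocation, the standard error with country in the model, relative to that without, is about √(1 − r), where r is the share of variance in the analysed variable that country explains. Section 2.10.1 works with before–after differences, so r refers to change and not to the level of the score.

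| r (assumed) | √(1 − r) | Standard error smaller by |
|---|---|---|
| 0 | 1.000 | 0% |
| 0.05 | 0.975 | 2.5% |
| 0.10 | 0.949 | 5.1% |
| 0.20 | 0.894 | 10.6% |

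Three countries need 3 − 1 = 2 degrees of freedom. With one value per family and 360 evaluable families, the error degrees of freedom fall from 360 − 8 = 352 to 350.

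**The case against.** **The block figure is a one-word slip.** Reading *group* for *block* removes the contradiction, and an article may leave the real block size to the full protocol. This is probably what happened, and it limits the consequence. It does not make the printed figure right: the article gives a block size, and that size conflicts with its own ratio.

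**Imbalance by country.** A reader might infer that the groups could end up badly unbalanced by country. The documents do not support that. Section 2.6 says the randomisation is stratified, and Section 2.1 fixes the number per group within each country, so a design balanced only overall is not the one described.

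**Bias.** A reader might also infer that omitting country biases the effect estimates. With 20 families per group in each country it does not; it costs precision and errs on the conservative side.

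**Change scores.** Constant differences in diet level between countries cancel in before–after differences, so a country share taken from raw scores would overstate the gain. This stands, and it is why the assumed range starts at zero.

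**An unseen analysis plan may add country.** It may. But the article names its model and lists the factors, and the stratified analysis in Section 2.10.2 examines differences in response without adjusting the primary comparison.

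**The two matters are unrelated.** Agreed: the missing country term does not follow from the block size, and each stands or falls alone.

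**Conclusion.** The point holds in two independent parts.

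1. The block statement is wrong as printed. That is certain from the arithmetic and rests on no assumption. That *block* was written for *group* is an inference, though a strong one. The planned 60 per group and 480 in total are unaffected.

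2. The primary model omits the implied stratum. That country is the stratum is inferred from Sections 2.1 and 2.7, since Section 2.6 does not name it. The loss is one of efficiency: standard errors would be 0 to 11% smaller with country included, if country explains 0 to 20% of the variance in change scores. That share is an assumption, and the true gain could be close to nothing. The term has a second use. Section 2.7 expects 25% drop-out and Section 2.8 replaces withdrawn families with the next eligible ones, so balance by country at randomisation need not survive to the final visit. A country term then guards against the resulting imbalance.

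**What to change.** **Section 2.6.** State 60 families per study group (20 in each country), name country as the stratification factor, and give block sizes that are multiples of 8 and fill 160. Sizes of 8 and 16, varied at random and made to close at 160 in each country, would do; varying them is sensible because research staff are not blinded. If the list has already been generated, report the strata and block size actually used instead. The cost is one sentence, with no change to the sample size.

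**Section 2.10.1.** Add country as a fixed factor in the primary MEDAS and KIDMED models. The cost is two degrees of freedom and no extra data, and it can be done whatever block size was used.

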### 2.7. Sample Size

The sample size was calculated based on differences in MD adherence score (primary outcome) measured by MEDAS and KIDMED questionnaires. The sample size was estimated using the analysis of variance (differences between 8 study groups). It was assumed that the alpha value would be equal to 0.05 and beta 0.20, exactly as reported in previous studies [61], with a common standard deviation equal to 1.19. The minimum group size needed to detect a minimum increase of 1 point in the intervention group’s MEDAS compared to the control group is equal to 45 families per study group (15 families per country). The total sample is, therefore, 45 × 8 = 360 families. However, assuming a 25% drop-out rate, the minimum group size is equal to 60 families per study group (20 families per country). Overall, 160 families will thus be recruited per country after obtaining the approval of the Ethics Committee of each recruiting center and written informed consent from parents and adolescents.

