### 2.5. Outcomes

The primary outcome will be adherence to the MD measured through the MEDAS and the KIDMED questionnaire score in parents and children, respectively. The MEDAS is an extension of a 9-point score developed in the Prevención con Dieta Mediterranea (PREDIMED) trial [42,43]. It consists of 2 questions about eating habits, 8 questions about the frequency of consumption of typical foods of the MD, and 4 questions about the consumption of foods not recommended in this diet. Each question is scored with 0 (noncompliant) or 1 (compliant), and the total score ranges from 0 to 14, so a score of 14 points means maximum adherence. The KIDMED score consists of 16 items with affirmative or negative answers, where there are 4 questions denoting a negative connotation to the MD and 12 questions denoting a positive connotation. A positive answer to questions denoting negative connotation is scored with −1, while positive connotation questions are scored with +1. The total score ranges from 0 to 12, so a score of 12 points indicates good adherence [44]. To avoid deviations in outcomes (such as physical activity or portions of food), surveys will be assessed by researchers during visits.

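### The sample size is said to rest on MEDAS and KIDMED but is worked out for MEDAS only, so 80% power with 5% error is not established for the two-score primary outcome.

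*Protocol article*

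**What the plan says.** Section 2.5 defines two scores as primary: "The primary outcome will be adherence to the MD measured through the MEDAS and the KIDMED questionnaire score in parents and children, respectively". It describes MEDAS as 14 items with a range of 0 to 14, and KIDMED as 16 items, four of them scored negatively, with a stated range of 0 to 12.

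Section 2.7 opens with the statement that both scores underlie the size: "The sample size was calculated based on differences in MD adherence score (primary outcome) measured by MEDAS and KIDMED questionnaires". It names an analysis of variance over 8 groups. On error rates it says: "It was assumed that the alpha value would be equal to 0.05 and beta 0.20". The variability is a single figure, "with a common standard deviation equal to 1.19", and the target is "to detect a minimum increase of 1 point in the intervention group’s MEDAS compared to the control group". The result is 45 families per group, raised to 60 for 25% drop-out. No KIDMED difference and no separate KIDMED SD appear.

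Section 2.10.1 says: "The error level of 0.05 will be set as a limit of statistical significance". It calculates mean differences between each intervention group and control for both scores. Bonferroni is attached to the post hoc tests of the three-factor ANOVA. Nothing is said about testing two scores.

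**The concern.** The opening sentence of section 2.7 claims more than the calculation delivers. KIDMED is a different instrument, with different scoring and in a different age group, so an SD and a target difference chosen for MEDAS cannot simply be carried over.

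The gap falls where much of the intervention acts. The educational programme is aimed at adolescents (section 2.3.2) and the snacks at children aged 3 to 11 (section 2.3.3). Both groups are scored by KIDMED. Every family must include a child under 12 and an adolescent (section 2.2).

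Two things are at stake. A null KIDMED result could be reported as a null from a trial with 80% power, which the article does not show. And with two primary scores, one error level and no rule linking them, a positive result on one score alone could be claimed at a nominal 5% that does not cover the pair.

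**Working it through.** **Inputs.** From section 2.7: difference 1 point (MEDAS), SD 1.19, alpha 0.05, power 0.80, 8 groups, 45 per group, 25% drop-out. Two-sided testing is assumed, since sidedness is not stated.

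**1. The plan's own figure.** Per-group size is n = 2 × SD² × (z for alpha + z for power)² / difference², with z for power = 0.842.
- Unadjusted: 2 × 1.19² × (1.960 + 0.842)² = 22.2, so 23.
- Bonferroni over 7 contrasts with control (0.05/7, z = 2.690): 35.3, so 36.
- Bonferroni over all 28 pairs (0.05/28, z = 3.124): 44.5, so 45.
- Omnibus F test over 8 groups, two groups 1 point apart and the other six midway: 42.

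The 45 matches one score over 28 pairs. The article does not state that basis; it is inferred from the match. 45 × 8 = 360 and 45 / 0.75 = 60 are correct. Every variant uses one score.

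**2. MEDAS power at 45 per group.** Pooled t test, df = 8 × 45 − 8 = 352, non-centrality 1 / (1.19 × √(2/45)) = 3.99.

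| Bonferroni tests | Power |
|---|---|
| 7 (control contrasts, one score) | 89.9% |
| 14 (control contrasts, both scores) | 85.3% |
| 28 (all pairs, one score) | 79.8% |
| 56 (all pairs, both scores) | about 74% |

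The normal approximation gives 80.6% for 28 pairs, which is why 45 is enough under that formula.

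**3. KIDMED power at 45 per group.** The SD is not in the article, so these are illustrations for a 1-point difference and one KIDMED value per family.

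| Assumed SD | 7 contrasts | 28 pairs |
|---|---|---|
| 1.5 | 68% | 51% |
| 2.0 | 37% | 22% |

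Over 28 pairs, the differences detectable with 80% power are 1.26 and 1.68 points. By the normal approximation, the largest SD that keeps 80% power for 1 point over 28 pairs is 1 / ((3.124 + 0.842) × √(2/45)) = 1.20, almost exactly the MEDAS figure.

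**4. Error and power over two scores.**
- Either score suffices, each tested at 0.05: 1 − 0.95² = 9.75% if independent, 9.1% at correlation 0.5, 7.0% at 0.9. Power to succeed on at least one score does not fall.
- Both must succeed: error stays at or below 5%. Joint power is below the power for either score alone. Even granting KIDMED the MEDAS inputs, with independent scores it is 0.899² = 81% over 7 contrasts and 0.798² = 64% over 28 pairs.

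**5. Factorial main effects.** With 180 v 180 families and no interaction, the standard error is 1.19 × √(2/180) = 0.125. The detectable MEDAS difference is 0.125 × (1.960 + 0.842) = 0.35 points at 0.05, and 0.125 × (2.241 + 0.842) = 0.39 at 0.025.

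**The case against.** The strongest reply is that nothing here shows the stated figures to be false. The arithmetic in section 2.7 is correct, and 80% is reached for MEDAS. The article names no success rule. An ordered test, a combined family score or a both-must-succeed rule would hold the error at 5%, and an analysis plan that is not shown may contain one. This stands. A reader might infer that the 80% and the 5% both fail, but they do not fail under the same rule: the either-score rule raises error without lowering power, and the both-scores rule lowers power without raising error.

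A second reply concerns the 28 pairs. Section 2.10.1 names differences between each intervention group and control, which is 7 contrasts. On that basis MEDAS power is 89.9%, and still 85.3% when Bonferroni covers both scores. A reader might infer that a second score necessarily pulls power below 80%. It does so over all pairs, not over control contrasts.

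A third reply is that the KIDMED figures rest on assumed SDs and one value per family, whereas each family supplies at least two KIDMED scores. If two siblings are averaged, SD 1.5 becomes 1.5 × √((1 + r)/2). For intra-family correlations r of 0.3 to 0.7 that is 1.21 to 1.38, and power over 28 pairs is 78% to 61% rather than 51%. This also stands. The documents do not show that the trial is underpowered for KIDMED, only that its power there is unsupported.

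Finally, 9.75% needs independent scores. Section 1 describes parental habits as dominant determinants of children's choices, so it is an upper figure.

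None of this supplies the missing KIDMED inputs or makes the opening sentence of section 2.7 accurate.

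**Conclusion.** The point holds in a limited form. Section 2.7 claims both scores and sizes one. The stated power is supported for MEDAS only, and the combination of 80% power and 5% error is not established for the primary outcome as section 2.5 defines it. If either score can carry a claim, the error is between about 7% and 9.75%, depending on correlation. If both are required, the cost falls on power, by an amount that cannot be fixed without a KIDMED SD and target difference. The KIDMED powers are illustrations under assumed SDs, and the 28-pair basis is an inference from the match to 45. This is worth correcting before results are read, but it does not call the enrolment target into question.

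**What to change.** In section 2.7, say that 45 families per group was sized for MEDAS only and name the comparisons it covers. Give the detectable KIDMED difference for a justified KIDMED SD, stating whether siblings are averaged.

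In section 2.10.1, name the rule for the two scores: for example Holm (0.025 for the smaller p-value, then 0.05), or a statement that both must succeed. Restate the power under that rule. At Holm's first step it is, for MEDAS, about 85% for 7 control contrasts or about 74% for all 28 pairs; these are lower bounds for Holm.

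If factorial main effects are quoted as a strength of the design, give about 0.35 MEDAS points at 0.05 and 0.39 at 0.025, say that no interaction is assumed, and note that neither figure adjusts for testing three components.

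The cost is some restated text and a slightly less favourable stated power. No additional families are needed.

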### 2.8. Criteria for Discontinuing or Modifying Allocated Intervention

If a severe or unanticipated adverse event (AE) occurs that may influence the risk/benefit ratio of this study, the principal investigator must report this to the ethics committee and permanently discontinue the family from the intervention. Participating families will be asked to report any AEs experienced during the entire intervention. For each AE, the onset date, intensity, relationship to the study product, action taken, and outcome will be recorded by researchers in accordance with the Medical Dictionary for Regulatory Activities (MedDra dictionary), Version 24.0 of MedDRA (Spanish), March 2021. In case of the suspicion of a major AE, such as an allergic reaction, the case will be referred directly to the study doctor, who will evaluate the symptoms and signs and adopt the necessary measures according to their severity.

In addition, the researchers can withdraw a family from this study if they consider that the family can no longer meet all the requirements of the study or if any of the procedures are considered possibly harmful for any of its members. Families participating in the study will be withdrawn if they meet any of the following criteria: (1) any circumstance that prevents them from performing the study procedures (i.e., using the educational materials or digital interactive tools and complying with the intake of the study products); (2) not attending study visits.

The losses and dropouts will be carefully recorded to ensure study reliability. The next participant who meets the eligibility criteria will replace the last participant who withdraws from the research until reaching the calculated sample size.

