The educational activities will be part of an educational program specially designed to improve adherence to the MD of adolescents. The program will be conducted outside of school hours during the 3-month intervention and will be previously designed during Phase 1 of this study under the umbrella of three selected topics: (1) Mediterranean Diet and Lifestyle: discovering cultures, foods, and tastes; (2) Mediterranean Diet: from a healthy diet to a sustainable dietary pattern; and (3) Food Lab: kitchens from research or cooking centers as experimental hands-on zones for the application of healthy and sustainable dietary patterns. At least two cocreation sessions will be organized in each study country, with adolescents assigned to the educational activity groups as cocreators. The World Cafe Methodology [37,38,39] will be applied, encouraging participants to talk to each other and discuss the three selected topics in small groups in a cozy café-style space hosted by researchers as moderators (Ms) and high-school teachers as facilitators (Fs). Each session will take around one-and-a-half hours and will be joined by about 12 adolescents and at least 2 teachers and 2 researchers who will be neutral and encourage participation. The adolescents will be divided into three tables (4 to 5 adolescents per table) and, at each table, one of the three selected topics will be discussed so that the adolescents will rotate around every 20 min to participate in the discussion of all the topics (Figure 3). The researchers will record all the conversations that take place on a smartphone and will also take written notes. Once all the discussion rounds have finished and after a coffee break, the entire group will meet again in plenary. The resulting activities from each table will be summarized by researchers who will bring down the number of generated ideas to a handleable minimum, focusing on those factors generally considered to be the most important. Finally, the participants will vote on the results to prioritize actions to be implemented as educational activities in the frame of the educational program. After the cocreation session, all the data will be gathered and analyzed by the researchers in each country. The codesigned activities will then be reprioritized by all participants via an online survey. Lastly, the researchers will select and develop the 12 most voted educational activities, with 4 per topic, to be implemented within the framework of the intervention study.

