In Phase 2, the selected families will attend V1 and V2 at the beginning and end of the 3-month intervention study, respectively. In V1, families will receive group training according to the different intervention groups: on the use of the S2H app, on snack consumption, and/or on the use of educational materials and activities. In addition, each family will be visited individually by expert nutritionists who will assess adherence to the MD through the MEDAS and KIDMED questionnaires for adults and children, respectively, and will take anthropometric measurements (body weight, height, BMI, waist circumference, blood pressure, and heart rate) for each family member. Nutritionists will also complete a medical history, including the use of medications and/or supplements. At the end of V1, time will be left for families to self-complete online questionnaires through the Microsoft Forms web-based application. The questionnaires will be adapted according to the age of the family members to assess socioeconomic, lifestyle, dietary, and environmental indicators. In addition, families will complete a 7DWR and report food expenses during the week after V1.

During the 3-month intervention, families will use the different educational components and products. They will be in continuous contact with the research team to ensure compliance and report any adverse events, particularly in children assigned to consume the snack products. In V2, each family will be visited individually, the same parameters as those in V1 will be measured by nutritionists, and data on socioeconomic, lifestyle, dietary, and environmental indicators will be self-reported by each family member by means of online questionnaires. A closing session of this study will be carried out by researchers once the intervention is completed to inform the families of the main results of the study.

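### The listed adverse-event record attributes events only to the snack product, and reporting stresses children assigned to snacks, so any harm count by component would be open to bias

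*Protocol article*

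**What the plan says.** Three statements in the protocol article bear on how adverse events are collected.

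- **Who reports.** Section 2.8: "Participating families will be asked to report any AEs experienced during the entire intervention". Section 2.4 adds that families stay in contact with the team during the intervention and will "report any adverse events, particularly in children assigned to consume the snack products".
- **What is recorded.** Section 2.8: "For each AE, the onset date, intensity, relationship to the study product, action taken, and outcome will be recorded". This is the only causality item listed.
- **Who knows the allocation.** Section 2.6: "the families and the research staff cannot be blinded to the intervention". Only the data analysts are masked.

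The meaning of study product can be read from Section 2.8 itself. Its first withdrawal criterion gives as examples "using the educational materials or digital interactive tools and complying with the intake of the study products". Products are things taken in; the educational materials and digital tools are listed beside them as something else.

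**The concern.** The trial is a full factorial of three components: app, education and snack. Its purpose is to separate what each contributes, alone and in combination. The stated adverse-event record follows only one of the three.

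The other two also involve food. The app issues weekly meal plans for every family member (Section 2.3.1). The education programme includes a Food Lab topic described as "kitchens from research or cooking centers as experimental hands-on zones for the application of healthy and sustainable dietary patterns". An event linked to a planned meal or a kitchen activity would be entered, but the listed fields offer no place to say so.

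Separately, the emphasis on children assigned to snacks follows the randomised assignment. Where families know their group, such a prompt can lead snack families to report more fully than others for reasons unrelated to true event rates.

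What is at stake is the component-level harm information. The Discussion plans to put forward the components with the greatest impact for national and regional health programmes, naming snacks and digital tools as examples. Readers of such a proposal will want to know what harms each component carried.

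**Working it through.** The article gives no figure for adverse events, so there is none to reproduce. The check compares the sections and counts the groups to which the field applies.

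**1. Groups and the causality field.** Three components, each present or absent, give 2 × 2 × 2 = 8 groups. Sections 2.6 and 2.7 set 60 families per group, so 8 × 60 = 480.

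| Groups | Families | Fit of a snack-only field |
|---|---|---|
| Control | 60 | No component assigned; nothing to attribute |
| App; education; app + education | 3 × 60 = 180 | No snack assigned; the assigned components have no field |
| Snack alone | 60 | Covers the assigned component |
| Snack + app; snack + education; all three | 3 × 60 = 180 | Covers the snack but not the other assigned component(s) |

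Groups without snacks: 60 + 180 = 240 of 480 families (50%). Groups in which at least one assigned component has no stated field: 180 + 180 = 360 of 480 (75%). The 60 control families belong in the first count but are not a gap in attribution, because they receive only basic guidelines.

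**2. Reporting across sections.** Section 2.8 covers all families and any event. Section 2.4 also says any event, then adds emphasis for children assigned to snacks. The two do not contradict each other: the second narrows attention, not eligibility. But the emphasis is tied to allocation, and Section 2.6 leaves families and staff aware of it. Unequal reporting is therefore possible. The text does not establish that it will occur.

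**3. Is a comparison planned?** Section 2.5 lists no adverse-event outcome. Section 2.10.1 states group comparisons for the adherence scores and none for adverse events. Any bias would affect a tabulation that the article does not describe.

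**4. How far unequal reporting could distort a count (illustration only).** Assume the same true event risk everywhere, with 240 snack and 240 non-snack families, and let non-snack families report a fraction d as completely as snack families. The apparent risk ratio is 1/d:

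- d = 0.90: 1/0.90 = 1.11
- d = 0.75: 1/0.75 = 1.33
- d = 0.50: 1/0.50 = 2.0

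The values of d are assumptions and come from nowhere in the documents. The ratios restate those assumptions. They show the direction and possible scale of the distortion, and are not evidence that it will happen.

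**The case against.** The strongest reply is that the article already has broad safety coverage. Every family is asked about any event throughout the intervention. Events in app and education families would be entered with onset, intensity, action and outcome, and could be counted by randomised group with no individual attribution at all. Withdrawal is allowed "if any of the procedures are considered possibly harmful for any of its members", which covers every component and every family member. Suspected major events go to the study doctor whatever the group. The list of fields is one sentence in a condensed article, and the full event form may be wider.

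Most of this stands, and it rules out several stronger readings that a reader might infer:

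- *Harms of the app and education would go unrecorded.* They would not; only their attribution is unstated.
- *The safety comparison between groups is biased, or the snack groups will show more events.* No such comparison is stated, and added emphasis for one group does not prove unequal reporting.
- *Limiting the allergy exclusion to children under 12 is a gap.* The exclusion concerns snack ingredients, and Section 2.3.3 gives the snacks only to children aged 3 to 11, so the two are consistent.

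The reply does not remove what the text positively says. The causality item is worded for the study product, and the reporting emphasis is worded by assigned group. Counting by group gets round the missing attribution only if collection is the same in all groups, and the wording of Section 2.4 works against that.

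**Conclusion.** The point holds in a limited form. As worded, the adverse-event record attributes events to the snack only. It has no referent in 240 of 480 families and leaves at least one assigned component without a field in 360 of 480. Reporting is stressed for children assigned to snacks in a trial where families and staff know the allocation, so ascertainment may differ by group, and any count of events by component would be open to bias of unknown size.

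This rests on reading study product as the snack, which Section 2.8's own usage supports, and on the listed fields reflecting the form in use. The primary outcome, the sample size and the stated analyses are untouched. It is a minor improvement that is worth making because it is cheap.

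**What to change.** - **Section 2.8:** replace relationship to the study product with relationship to each assigned study component (app, education, snack), with not applicable for components that were not assigned.
- **Section 2.4:** remove the emphasis on children assigned to snacks. State that the same adverse-event question is asked, for every family member, at the same contacts and at V2 in all eight groups.
- **Reporting:** with collection made uniform, tabulate events by randomised group.

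The cost is a few more fields on the event form, one standard question at contacts and a visit that already take place, and slightly more events to record in the non-snack groups. The sample size, the visit schedule and the primary analysis do not change.
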